#### Comparative Analysis of the Gut Microbiome Between Healthy Participants and Patients With PD

Differences in gut microbiome between healthy participants and patients with PD will be determined by testing the acquired data for normality and performing a parametric test with an independent *t* test if the population is normal or a nonparametric test with the Mann-Whitney *U* test if the population is not normal.

### Safety Analysis

For all adverse events that occurred during treatment, the frequency of adverse events will be analyzed according to whether they were associated with treatment or not. The number and proportion of participants with at least one adverse event, 95% CI, and the number of occurrences will be presented.

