#### Intradermal Acupuncture Treatment

After acupuncture and moxibustion treatments are completed, intradermal acupuncture (Press Needle, Dongbang Medical Co, Ltd) will be attached to the bilateral Yanglingquan (GB34), Zusanli (ST36), and auricular Shenmen. Patients will be instructed to frequently apply acupressure to the attachment area.

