#### Evaluation of Gut Microbiome–Related Metabolites and Gut Microbiome Change

Blood samples will be used to assess changes in gut microbiome–related metabolites. Blood will be collected from participants after an 8-hour fast before blood collection, and changes in metabolites will be determined using liquid chromatography-mass spectrometry and gas chromatography-mass spectrometry analyses. Western blotting will be applied to confirm changes in strain-derived factors in the blood of patients with PD. Participants’ fecal samples will be used to analyze the composition of the gut microbiome using 16S rRNA sequencing and fecal microbiome transplantation to assess the correlation between gut microbiome and response to acupuncture treatment. A small amount of feces will be collected using 4N6 FLOQSwabs (Copan Diagnostics Inc). For participants with PD, 2-3 g of feces will be collected using a Stool Collection Tubes With DNA Stabilizer (Invitek Diagnostics) for fecal microbiome transplantation. A FastDNA SPIN Kit for Feces (MP Biomedicals) will be used to isolate DNA from feces for DNA extraction and sequencing. DNA will be subjected to polymerase chain reaction targeting the V3-V4 variable region of bacterial 16S rRNA as a template, followed by sequencing library construction and sequencing reactions on the MiSeq Platform (Illumina, Inc). Sampling will be conducted at day 0, 6 weeks, 12 weeks, and 20 weeks in participants with PD and after screening in healthy participants.

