### Safety Assessments and Monitoring

At each visit, the participants’ subjective and objective adverse events will be investigated and classified into mild, moderate, and severe as follows: mild, participant feels little to no discomfort and symptoms interfere little with usual activities of daily living (ADL), most likely not requiring treatment; moderate, participant may experience discomfort that interferes with usual ADL, which may allow the participant to continue the study but may require treatment; severe, participant feels very uncomfortable, interfering with usual ADL, unable to continue participating in the study, and may require treatment or hospitalization. The causal relationship between reported adverse events, acupuncture treatments, and blood collection will be categorized by the Korean medicine doctor in charge as follows: more than 90%, definitely; 70%-90%, probably; 50%-70%, possibly; 30%-50%, probably not; and less than 10%, definitely not.

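### As written, the adverse event frequency analysis stops at the end of treatment, although events are collected, and efficacy is analyzed, to week 20

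*Protocol article*

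**What the plan says.** **Collection.** Safety Assessments and Monitoring states: "At each visit, the participants’ subjective and objective adverse events will be investigated". It adds: "The causal relationship between reported adverse events, acupuncture treatments, and blood collection will be categorized". Blood collection is therefore a recognized source of harm in this study, separate from needling.

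**Visits.** Under Evaluation of Gut Microbiome–Related Metabolites and Gut Microbiome Change: "Sampling will be conducted at day 0, 6 weeks, 12 weeks, and 20 weeks in participants with PD". The clinical scales follow the same four time points. Interventions gives a treatment course of 12 weeks and 24 sessions.

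**Analysis.** Safety Analysis has two sentences. One sets the window: "For all adverse events that occurred during treatment, the frequency of adverse events will be analyzed", split by relation to treatment. The other lists the summaries and names no window: "The number and proportion of participants with at least one adverse event, 95% CI, and the number of occurrences will be presented".

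**Efficacy window.** Overview of Statistical Analysis computes change from baseline to the end of treatment and to follow-up. Analysis for Changes in Clinical Outcomes tests change to weeks 6, 12 and 20.

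**The concern.** The stated analysis rule is narrower than the data the protocol collects. It is also narrower than the period over which benefit is examined. The Discussion hypothesizes a lasting improvement after treatment, and the week 20 visit supplies the outcome data for that. If safety is summarized only to week 12, harm and benefit are shown over different periods. Events found at the week 20 visit would be recorded and causality-rated, yet have no place in the planned frequency table.

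This is a rule the article states, not a detail it leaves open. The Discussion concedes other safety limits (no independent adjudication, no standardized grading) but not this one.

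**Working it through.** The plan gives no adverse event rate and no figure tied to this point, so there is nothing to reproduce. The check has three parts: the meaning of the window, the share of follow-up it leaves out, and a conditional illustration.

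**1. Meaning of the window.** The Abstract and Study Design list four time points: day 0 (before treatment starts), week 6 (labeled as during treatment), week 12 (end of treatment) and week 20 (two months later). In the document's own usage, then, week 20 lies after treatment. The restriction in Safety Analysis covers weeks 0 to 12.

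**2. Share left out (patients with PD).**
- Follow-up: 20 − 12 = 8 weeks, and 8/20 = 40% of post-baseline time.
- Scheduled blood draws: 4 per patient, of which 1 (week 20) comes after treatment. With 60 patients at full attendance, that is 60 of 240 draws (25%).

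**3. Illustration on assumed rates.** Let p12 be the proportion with at least one event by week 12. Let f be the follow-up hazard relative to the on-treatment hazard. With a constant hazard within each period:

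P20 = 1 − (1 − p12)^(1 + f × 8/12)

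For example, p12 = 10% and f = 1 gives 1 − 0.90^1.667 = 16.1%.

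| Assumed p12 | f = 0 | f = 0.25 | f = 0.5 | f = 1 |
|---|---|---|---|---|
| 5% | 5.0% | 5.8% | 6.6% | 8.2% |
| 10% | 10.0% | 11.6% | 13.1% | 16.1% |
| 20% | 20.0% | 22.9% | 25.7% | 31.1% |
| 30% | 30.0% | 34.0% | 37.8% | 44.8% |

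In counts for n = 60 with exact (Clopper-Pearson) 95% intervals:
- p12 = 10%: 6/60 (3.8% to 20.5%) by week 12. At f = 1, 60 × 0.161 = 9.7, about 10/60 (8.3% to 28.5%), by week 20.
- p12 = 20%: 12/60 (10.8% to 32.3%) by week 12. At f = 1, 60 × 0.311 = 18.6, about 19/60 (20.3% to 45.0%), by week 20.

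**The case against.** The strongest reply is that exclusion is inferred. The sentence promising the proportion with at least one event and its 95% CI names no window, the restricting phrase is never formally defined, and the schedule for patients with PD (Table S1) is not shown. This stands in part. Collection at week 20 rests on the words about each visit, and the second sentence could be read without a limit. But it directly follows the restricted sentence and most naturally inherits its window. If it does not, two adjacent summaries cover different periods without saying so. Either way the section needs correcting.

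Four stronger readings are tempting, and the documents do not support them:

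- **Events after the last blood draw are dropped by this rule.** The last draw is at the week 20 visit, and no later visit is described. Events arising afterward are a limit of collection, not of the analysis window.
- **Press-needle events after the final session are excluded.** The protocol says: "After acupuncture and moxibustion treatments are completed, intradermal acupuncture" is attached, and it counts this as one of the treatments. Wearing time is not given. An event while the needles are still in place may well count as occurring during treatment.
- **Events in the 20 healthy participants are collected and then discarded.** Their schedule (Table 1) has no adverse event row, so collection in this group is itself uncertain.
- **The reported proportion is too low by a known amount.** A constant 2% per week would give 1 − exp(−0.24) = 21% by week 12 and 1 − exp(−0.40) = 33% by week 20, about 13 versus 20 of 60. That assumes the same hazard in eight untreated weeks as during 24 sessions. If events come mainly from the procedures, the true difference is smaller, and with no follow-up hazard it is zero. A treatment-period proportion is also a legitimate quantity. The fault is that it is the only one planned.

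It is also fair to note that Sample Size calls the study exploratory and not meant to validate an effect. The point about unequal windows therefore concerns what is analyzed, not a claim of proven efficacy.

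**Conclusion.** The point holds in a limited form. Followed as written, Safety Analysis leaves out of the frequency analysis any event in a patient with PD that begins in weeks 12 to 20, including any from the week 20 draw. That is 8 of 20 weeks of observation and one of four scheduled draws per patient, while efficacy is analyzed to week 20.

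The effect on the reported proportion cannot be known from the documents. For a follow-up hazard between none and the on-treatment level, it runs from no change up to 6.1 percentage points at an assumed 10% by week 12 (16.1 − 10.0), and up to 11.1 points at an assumed 20% (31.1 − 20.0).

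The conclusion rests on two readings: that the article uses its treatment-period wording consistently, and that collection at each visit includes week 20. No stated figure in the plan is wrong. It is worth correcting because the rule omits data the study was set up to collect.

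**What to change.** In Safety Analysis, replace the restriction with an explicit window: all adverse events collected in patients with PD from the first study procedure to the week 20 visit. Report the number and proportion with at least one event, the 95% CI and the number of occurrences for the treatment period (weeks 0 to 12), the follow-up period (weeks 12 to 20) and overall. State that the same windows apply to both sentences of the section. Starting at the first procedure also settles how events from the day 0 draw are counted, since the article places that visit before treatment. List separately any blood-draw events recorded in healthy participants.

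The cost is wording and one extra table column. Results reports that observation has ended and analysis is under way, so the change needs no new visits. Setting the window before the safety results are reported also avoids choosing it after seeing the events. The downside is a possibly slightly less favorable overall rate.

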### Ethical Considerations

The study protocol was approved by the institutional review board of Kyung Hee University Korean Medicine Hospital (KOMCIRB 2021-07-002-001; approved on September 14, 2021). This study is conducted in accordance with the principles of the Declaration of Helsinki. Participants who wish to participate receive an explanation of the consent form from the study researcher and give written consent of their own free will. All data from participants will be simultaneously recorded in an eCRF with an identification code rather than the participant's name to protect personal information.

## Results

The study was supported by the National Research Foundation of Korea, funded by the Ministry of Science and ICT (no. 2022M3A9B6017813). Recruitment for the registry commenced on October 15, 2021, and was scheduled to end on September 13, 2023. Recruitment began on October 22, 2021, and as of February 19, 2025, participant recruitment and observation ended, and data analysis is being conducted.

## Discussion

The clinical efficacy of acupuncture for PD has been consistently reported. Pereira et al [40] analyzed 17 randomized controlled trials (RCTs) on acupuncture for PD published in English between January 2011 and July 2021 and found that the combination of acupuncture and conventional treatment was superior to conventional treatment alone for motor and nonmotor symptoms of PD. Similarly, Lee et al [15] analyzed 16 RCTs, investigating 15 acupuncture treatments and 1 moxibustion treatment, published between 2008 and 2013, and comparing acupuncture or moxibustion with conventional therapies such as dopamine, found that all but one showed significant improvement in the acupuncture or moxibustion treatment group. In particular, for nonmotor symptoms of PD, for which effective treatments remain lacking, Li et al [41] reported through an analysis of 27 RCTs that acupuncture treatment could improve depression, quality of life, cognition, total mentation, behavior and mood, and ADL in patients with PD. Based on these clinical study data, the Clinical Practice Guideline of Korean Medicine for Parkinson's Disease recommended combination treatment of acupuncture and anti-Parkinsonian drugs for patients with PD, while moxibustion treatment may also be considered [42].

Attempts to identify the mechanisms of action of acupuncture in PD to support clinical data are still ongoing. Previous experimental studies using PD models have shown that acupuncture exerts neuroprotective effects through activation of neuroprotective agents such as brain-derived neurotrophic factor, glial cell line-derived neurotrophic factor, and cyclophilin A [43], effective in PD symptoms by inducing neuromodulation, thus controlling inflammation and brain functional connectivity [44,45], and p53 signaling-mediated neuroprotective effect [46]. However, these opinions are insufficient to reflect the systemic nature of PD and do not fully explain the improvement in nonmotor symptoms associated with acupuncture.

The gut-brain axis mechanism of PD stemmed from the perspective that PD should be managed and treated as a systemic disease [7]. Braak et al [47] observed that unknown pathogens invade the body through the intestines, while Lewy bodies selectively move from the intestines along the central nervous system and metastasize to the brain; based on the hypothesis that the motor and nonmotor symptoms of PD appear according to this metastasis, they proposed the Braak stage, which divides this process into 6 stages. This finding has drawn attention to the role of the gut in the pathology of PD. Recently, it has also been hypothesized that PD is divided into brain-first and gut-first, based on the division of positive and negative rapid eye movement sleep behavior disorder in the prodromal phase [48]. The fact that gastrointestinal symptoms, such as constipation, appear very early in the prodromal phase [49] and that 60%-80% of patients experience gastrointestinal symptoms [50] may also support the gut-first PD hypothesis.

Imbalances in the gut-brain axis caused by gut microbial dysbiosis can lead to increased inflammatory signaling and epithelial permeability, both of which are known to play an important role in neurodegenerative diseases such as PD [19]. The neurotoxin 1-methyl-4-phenyl-1,2,3,6-tetrahydropyridine increases α-synuclein and influences compositional changes in gut microbiome, including the phylum Proteobacteria [51]. Gut microbiome dysbiosis also induces microglial activation and neuroinflammation, which may promote α-synuclein overexpression, resulting in motor dysfunction [52,53]. Taken together, these results suggest that regulation of gut microbiome may have significant potential as a key treatment for PD, functioning through modulation of the gut-brain axis.

In the TEAM theory, the functional connection and communication between acupoints, the brain (ancient heart), and the gut is clinically important [54]. Based on the traditional theory, a previous review study [55] has reported that acupuncture has an effect on various diseases, including metabolic diseases, gastrointestinal diseases, mental disorders, and nervous system diseases, by regulating gut microbiome. Further, a large number of experimental studies on the relationship between PD and gut microbiome have been published recently, and the number is rapidly increasing [55]. In a previous experimental study including a PD model [19], we found that acupuncture treatment with GB34, which has been shown to exert neuroprotective effects on the brain, and ST36, which has been shown to enhance digestive function, improved motor function and anxiety, and increased the levels of dopaminergic fibers and neurons in the striatum and substantia nigra, increased the diversity of gut microbiome (alpha-diversity) and restored a gut microbiome to a composition more similar to that of robust controls (beta-diversity) compared with that noted in the PD group, in addition to restoring the increased levels of proteobacteria at the phylum level, suggesting that acupuncture exerts effects on improving gut microbiome imbalances. In another previous study [56], we conducted a clinical study to investigate whether acupuncture treatment for 2 weeks could effectively improve motor symptoms of PD using the UPDRS II+III in 73 patients with PD. This study showed that both the acupuncture treatment group and the control group showed improvement in motor function, with no significant intergroup difference; however, at the follow-up of 2 months after the end of treatment, the acupuncture treatment group continued to maintain these improvements in symptoms, while the control group reported a regression. Considering the results of these previous experimental studies, we hypothesized that acupuncture in this clinical study affected changes in gut microbiome to improve PD symptoms in a sustainable manner. To verify this hypothesis, we present the protocol of this study to explore changes in gut microbiome caused by acupuncture and moxibustion in patients with PD and explore its association with improvement in clinical symptoms of PD.

This protocol has limitations. First, as this study was designed as a single-group, prospective observational study with a primary focus on analyzing pre-post changes of patients with PD, a control group of healthy participants was included for baseline comparison rather than incorporating a control group within the PD cohort. This limits the internal validity of the intervention findings, as changes may be influenced by natural disease progression or placebo effects rather than the treatment itself. Second, although the sample size was determined based on feasibility rather than statistical power calculations, 60 patients with PD and 20 healthy participants may limit the reliability and generalizability of both within-group and between-group comparisons and increase the risk of type II error. Third, as no blinding was applied, the use of subjective, patient- and clinician-reported outcomes such as MDS-UPDRS, PDQ-39, and MYMOP increases the risk of detection and expectation bias, potentially compromising causal inference in this single-arm design. Fourth, adverse events are assessed by the treating Korean medicine doctors without independent adjudication or standardized grading criteria, which may limit the objectivity and consistency of safety reporting in this study. To address these limitations, future studies should adopt an RCT design with an adequately powered sample size, blinding procedures, and standardized outcome and safety assessments to enhance the internal validity, causal inference, and generalizability.

This study has limitations that must be weighed when interpreting the findings. Nutritional management is recommended for patients with PD, including dietary distribution to optimize levodopa absorption, dietary interventions for the improvement of nonmotor symptoms, and regular monitoring of food intake [57]. This leads to differences in dietary habits between PD patients and robust people, with PD patients showing higher protein and higher fiber dietary habits than robust people [58]. Fibers activate various beneficial microbiomes and suppress harmful species, and protein also has a significant impact on the gut microbiome [59]. Since this study does not investigate the nutritional intake of PD patients and healthy individuals, the influence of dietary differences should be considered when comparing the gut microbiome results between the two groups. Furthermore, levodopa dosage may affect gut microbiome composition [60]. Although this study investigates levodopa dosage in PD patients as part of clinical outcomes, it does not exclude the potential confounding effect of dosage adjustment on the gut microbiome. Therefore, any significant changes in levodopa dosage should be taken into consideration in the results.

The study will generate data on the effects of acupuncture and moxibustion on gut microbiome of patients with PD and explore its association with improvement in clinical symptoms. If the study results demonstrate that acupuncture and moxibustion change the gut microbiome in patients with PD, it will be the first clinical evidence to support a microbiome-gut-brain axis mechanism for acupuncture and moxibustion treatment of PD, ultimately contributing to the potential of acupuncture and moxibustion as an alternative treatment for PD.

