## Methods

### Study Design

This protocol describes a single-group, prospective, observational study aiming to analyze differences in gut microbiome between patients with idiopathic PD and healthy participants, to observe changes in gut microbiome after 12 weeks of acupuncture and moxibustion in patients with PD, and to correlate these changes with changes in motor and nonmotor symptoms of PD that were altered by acupuncture and moxibustion treatment. The gut microbiome patterns at baseline in healthy participants and screened patients with PD will be analyzed to determine whether the gut microbiome of patients with PD is different from that of healthy participants. Patients with PD will be treated with acupuncture, moxibustion, and intradermal acupuncture twice a week for 12 weeks, yielding a total of 24 sessions. The motor and nonmotor symptoms of PD and gut microbiome changes in response to acupuncture and moxibustion will be compared before starting treatment (day 0), during treatment (6 weeks), at the end of treatment (12 weeks), and 2 months after the end of treatment (20 weeks). The correlation between motor and nonmotor symptoms of PD changed by acupuncture and moxibustion treatment and changes in gut microbiome will be analyzed. The enrollment, interventions, and assessments of patients with PD are summarized in Table S1 in Multimedia Appendix 1. A schematic of the study process is shown in Figure 1. Healthy participants will be assessed for motor and nonmotor symptoms of PD and gut microbiome after screening. The enrollment and assessment of healthy participants are summarized in Table 1. Kyung Hee University Korean Medicine Hospital, Seoul, Republic of Korea, will serve as the study site. The study protocol was registered with the Clinical Research Information Service (KCT0006669) on October 15, 2021. This protocol was reported in accordance with the SPIRIT (Standard Protocol Items: Recommendations for Interventional Trials) guidelines (Multimedia Appendix 2).

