#### Changes in Gut Microbiome–Related Metabolites and Gut Microbiome

Differences in microbiome at each time point will be measured using weighted-unweighted UniFrac distance metrics and subsequently tested using analysis of similarity (ANOSIM). Correlations of clinical outcomes and treatment effects with key microbiomes will be analyzed using Spearman rank correlation analysis, with *P*<.05 considered significant. Principal component analysis will be applied to analyze metabolite distribution in the sample. Partial least squares-discriminant analysis will be applied to identify differences between patients with PD and healthy participants when analyzing metabolite distributions. Selected gut microbiome and metabolite changes will be analyzed by 1-way repeated measures ANOVA, with significant differences between time points determined at *P*<.05. The pathway analysis or enrichment analysis will be performed to analyze the metabolic pathways of the selected metabolites. The Kyoto Encyclopedia of Genes and Genomes database [39] will be used to identify interactions between metabolites. Receiver operating characteristic analysis will be conducted to confirm whether the selected metabolites reflect the representativeness of the disease or treatment.

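### The Discussion would take any demonstrated microbiome change as evidence for the gut-brain mechanism, but no named over-time analysis shows whether patients move toward or away from the healthy participants

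*Protocol article*

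**What the plan says.** All references are to the protocol article.

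- **Conclusion drawn from change.** The last paragraph of the Discussion states: "If the study results demonstrate that acupuncture and moxibustion change the gut microbiome in patients with PD, it will be the first clinical evidence", and goes on "to support a microbiome-gut-brain axis mechanism for acupuncture and moxibustion treatment of PD".
- **Rationale.** Earlier, the Discussion argues from dysbiosis in PD. It reports that in the group's animal study acupuncture "restored a gut microbiome to a composition more similar to that of robust controls (beta-diversity"). The clinical hypothesis is then introduced with reference to those experimental results, and is that acupuncture alters the microbiome so as to improve symptoms durably.
- **Role of the healthy participants.** Study Design: "The gut microbiome patterns at baseline in healthy participants and screened patients with PD will be analyzed to determine whether the gut microbiome" of patients differs from theirs. The limitations paragraph of the Discussion: "a control group of healthy participants was included for baseline comparison rather than incorporating a control group within the PD cohort".
- **Sampling.** "Sampling will be conducted at day 0, 6 weeks, 12 weeks, and 20 weeks in participants with PD and after screening in healthy participants".
- **Over-time analysis.** "Differences in microbiome at each time point will be measured using weighted-unweighted UniFrac distance metrics", followed by an ANOSIM test. Selected taxa and metabolites are tested by one-way repeated measures ANOVA at P<.05.
- **Link to symptoms.** The same section plans Spearman rank correlation of clinical outcomes and treatment effects with key microbiome features.
- **Status.** The Sample Size section calls the study exploratory and says it does not aim to validate the treatment effect statistically.

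**The concern.** The argument for a gut-brain mechanism starts from an imbalance in PD and from animal data in which treatment moved the microbiome back toward controls. A shift further from healthy would fit that argument poorly. A sideways shift through diet, medication or the passage of time would say little about it. Yet the closing sentence is satisfied by either, because its only condition is that the microbiome changes.

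A healthy reference group is available, but none of the named over-time analyses uses it. The main conclusion could therefore be written from a result whose direction was never examined. With no untreated PD group, direction relative to healthy and association with symptoms are two of the few features that could make an observed change more or less consistent with the proposed mechanism.

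**Working it through.** **Plan's own figure.** There is none to reproduce. The 60 patients and 20 healthy participants were set by resources and expert advice, with no effect size, SD or power.

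**Step 1: what each named analysis can show**

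| Analysis | Samples used | Direction relative to healthy? |
|---|---|---|
| UniFrac + ANOSIM across time points | PD visits | No |
| Repeated measures ANOVA, selected taxa and metabolites | PD visits | No |
| t test or Mann-Whitney, PD vs healthy | Baseline, per Study Design and the limitations paragraph | Shows the starting gap only |
| PLS-DA and ROC | Separate groups or classify | No test of movement |
| Spearman with clinical outcomes | PD | Signed, but relative to symptoms |

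**Step 2: why the over-time tests are unsigned.** For day 0 against week 12 with full data there are 60 + 60 = 120 samples and M = 120 × 119 / 2 = 7,140 pairwise distances. ANOSIM computes R = (mean rank between visits − mean rank within visits) / (M/2). Every distance is between two patient samples. No healthy sample enters, so R cannot depend on where the healthy group lies. The ANOVA F statistic uses squared deviations of visit means from the grand mean, so reversing the sign of every change leaves it the same.

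**Step 3: illustration on assumed data.** None of these settings comes from the protocol: 10 Gaussian features, a PD-minus-healthy gap of 0.8 SD on 5 of them, within-patient correlation 0.5, Euclidean in place of UniFrac distance, 60 PD and 20 healthy, 200 runs per scenario. By week 12 the gap closes by 50%, widens by 50% or stays. ANOVA uses one feature over four visits. The last two columns concern the paired change from day 0 to week 12 in distance to the healthy centroid.

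| Scenario | ANOSIM rejects | ANOVA rejects | Distance-to-healthy test rejects | Mean change in distance |
|---|---|---|---|---|
| Toward | 86.5% | 89.0% | 73% | −0.32 |
| Away | 87.0% | 87.5% | 98% | +0.51 |
| None | 0% | 3% | 5% | −0.01 |

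The Monte Carlo standard error of a rate near 87% is √(0.87 × 0.13 / 200) = 0.024. The toward-away differences of 0.5 and 1.5 points are therefore noise, as Step 2 requires. The sign of the distance change separates the scenarios. Its size is not symmetric (−0.32 against +0.51 for shifts of equal length), because distance is not a linear measure.

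**Step 4: what the added analysis could detect.** Assume two-sided alpha 0.05 and 80% power, with normal quantiles 1.960 + 0.842 = 2.802.

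- Paired change, n = 60: 2.802 / √60 = 0.36 SD of the within-patient differences, before dropout and ignoring error in the healthy reference.
- Baseline gap on one feature, 60 vs 20: 2.802 × √(1/20 + 1/60) = 0.72 SD.

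The second figure marks a limit. If the true gap on a feature is well below 0.72 SD, the direction toward healthy will be poorly defined for it.

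**The case against.** The strongest reply has five parts.

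1. **The stated hypothesis is anchored on symptoms.** The objectives are a baseline comparison, change after treatment, and correlation of that change with symptoms. Restoration toward controls is reported as a result of the animal study. This stands. A reader might infer that the study set out to test whether treatment corrects the imbalance and cannot answer its own question, but no stated objective says that. A symptom-linked shift in another direction would not contradict the hypothesis as worded.
2. **The Spearman analysis supplies a sign.** It does, so unqualified change is not the whole plan, and the sentence just before the quoted one mentions association with clinical improvement. But the quoted sentence does not make its conclusion depend on that association.
3. **There is no decision rule.** This also stands. A reader might infer that a shift away from healthy would be declared a success. The study is exploratory and defines no success criterion. The limitations paragraphs warn of natural progression, placebo effects, diet and levodopa changes. Direction is not among the limits they admit.
4. **Direction can be read from visit means set beside healthy values, and detail may sit in an analysis plan that is not shown.** This is fair for individual taxa. It does not work for ANOSIM, and it does not alter what the article itself concludes from change. The phrase about differences at each time point could also mean PD versus healthy at every visit. However, it stands under a heading about changes, two other sections assign the healthy group to baseline, and an unsigned test at each visit would still not test the change in distance.
5. **Healthy is an imperfect target.** The Discussion says that diet differs between patients and healthy people and was not measured, so a change in diet or medication could move patients toward the reference without any treatment effect. This stands, and it is why reduced distance should not be the only admissible support.

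**Conclusion.** The point holds as a mismatch between the closing inference and the named analyses. The sentence requires only change, the rationale is restoration toward controls, and no named over-time analysis distinguishes movement toward healthy from movement away. That the named tests are unsigned follows from their construction and needs no assumption. The rejection rates only illustrate it and depend on the assumed data.

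The documents do not show what share of unspecific drift would go the wrong way. A figure of one half would follow only from assuming that drift has no preferred direction. Nor would movement toward healthy establish a treatment effect, since there is no untreated PD group. The correction improves an exploratory study's main inference at low cost. It does not touch MDS-UPDRS, the named primary outcome.

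**What to change.** **Add a supportive analysis.** For each patient and visit, compute the mean weighted and mean unweighted UniFrac distance to the 20 healthy samples. Report the within-patient change from day 0 to weeks 6, 12 and 20 with a paired test and CI. That is 3 × 2 = 6 estimates; show all of them. Beside these, report the signed change in taxa and metabolites that differ between PD and healthy at baseline. Recruitment and observation had ended by February 19, 2025 and analysis was under way, so date the addition and label it as specified after data collection.

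**Reword the closing paragraph of the Discussion.** Report an undirected change as descriptive. Claim support for the mechanism only where the change is toward healthy, associated with symptom improvement, or both, and still subject to the admitted limits: no untreated PD group, unmeasured diet, levodopa changes.

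**Cost.** One derived variable per metric and no new samples. The drawbacks should be stated:

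- The analysis is post hoc.
- A reference from 20 people is imprecise. The same reference serves every visit, so much of that error should cancel in the paired change, but a paired CI treats the 20 as fixed.
- Distance also reflects dispersion, so a change in spread can look like a shift.
- Taxa picked because they differ at day 0 will tend to drift back toward healthy through regression to the mean, since selection and change share the day-0 sample. Read the signed taxon changes with that in mind and give more weight to the distance measure, which involves no such selection.
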